### Sample size determination

The effect size to be expected is uncertain as no study so far has implemented a combined intervention of music and electrical stimulation in DOC patients. We assume it to be in the medium-to large range (i.e., Cohen’s d between 0.5 and 0.8). We aim to achieve 80% power (*f* = 0.30) in a repeated-measures analysis of variance (*a* = 0.05, power (1-b) = 0.80) with condition as between-subject factor (tES combined with music stimulation vs. sham stimulation, and noise vs. music stimulation and sham stimulation), and time (pre-intervention, post-intervention and post-placebo), as within-subject factor. Power calculations (using G* Power 3) indicate that a valid sample size of *n* = 10 per group will result in 80% statistical power if the effect is *d* = 0.68, which is in the medium-to-large range. This results in a total sample size of *n* = 30.

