#### Music stimulation

Music stimulation will consist of passive listening to 8 musical tracks. Four tracks will be chosen based on the musical preferences of each patient. Preferences will be derived from a musical anamnesis, namely a structured interview with the caregiver to know the patient’s lifestyle history and musical taste, conducted by the neuropsychologist. The outcome of this interview will help to tailor an individual treatment with familiar and self-relevant music, as previously done [47, 48]. The other four tracks are fixed and chosen by us based on previous literature: Adios Nonino by A. Piazzolla (used in several brain imaging studies); the Prelude in C major by J. S. Bach and the Prelude in C minor from the “Well-tempered Clavier”–I vol.; and a “atonal” version of the C major Prelude (also from the “Well-tempered Clavier”) where the original interval relationships between each note have been altered while maintaining the ascending/descending trend and temporal values of the notes. The two preludes and the atonal version have been used in previous neurophysiological and behavioural studies of auditory memory in healthy and elderly adults [49–52]. For optimising the stimulus variation, the eight tracks will be organized in playlists always alternating based on familiarity (the favourite song alternates a fixed one), on acoustic features (e.g., a track containing lyrics alternates an instrumental one) and emotional content (an arousing track alternates a relaxing one).

All patients will undergo standard physiotherapy rehabilitation treatment, according to the hospital guidelines, for one hour a day, 5 days a week. In addition, most of these patients are treated with specific drug therapy (such as, amantadine, citicoline, dopamine, etc.) in order to increase the level of consciousness. During data analysis these aspects will be considered and treated as necessary. Specifically, drug treatment and doses will be inserted as confounding factors and covariates in the ANOVAs.

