### Data analysis

The SPSS 23.0 statistical software will be used for the data analysis. All the statistical hypotheses will be tested by two-side test, with statistically significant test level set at 0.05 and the confidence interval estimation to 95%.

The aim of our study is to evaluate the effects of the treatments in the various patient groups on the primary and secondary outcomes. Descriptive analysis of the data will allow us to identify the characteristics of the groups. Comparison of demographic and clinical characteristics of the groups will be performed using one-way ANOVA for continuous variables and the Chi-square test for categorical variables. Considering the crossover and longitudinal aspects, primary analyses will focus on behavioural changes at group level, comparing the treatments. Moreover, at the individual level, we will analyse the differences between pre-treatments and post treatments data.

As for the primary outcomes, we will measure the effects of the intervention on the following measures (two neurophysiological and two clinical and behavioral): (i) power spectra of frequency band extracted from the EEG recordings; (ii) auditory evoked responses, extracted from the EEG recordings; (iii) behavioural responses of DOC patients, measured through CRS-R.

Baseline characteristics and carryover effect will be analysed between the three sequences using ANOVA and chi-square test. By including the order of intervention as a covariate, we aim to determine whether the sequence in which participants receive the interventions impacts the observed outcomes. To assess the presence and magnitude of the washout effect, we plan to incorporate appropriate statistical methods into our analysis, such as comparing outcomes during the washout period to those observed during active treatment phases. To this end, we will use repeated measures ANOVA considering time (before, during, and after the washout) as the independent variable, with behavioral measurements as the dependent variables.

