For the secondary outcome we will measure the effects of the treatments on caregivers’ depression, anxiety, psychophysiological symptoms, grief, strain and quality of life in order to evaluate the effectiveness in reducing the caregiver’s burden and psychological distress. Repeated-measures analysis of variance, as well as post-hoc paired *t*-tests will be conducted to assess the effects of the treatments over time on N1, P1, and P2 amplitudes and latencies, as well as level of consciousness. All these primary outcome variables will be analysed separately, using parametric or non-parametric tests for continuous and categorical variables respectively.

For the behavioural outcome, we expect an improvement of level of consciousness, as measured by CRS-R.

For the caregiver’s burden, we expect a positive effect of this new treatment protocol on caregiver’s wellbeing, with a decrease of psychological distress.

For neurophysiological outcome measures, we expect to obtain in DOC patients an increased EEG power spectrum in slow frequency bands, following a previous study [67] showing a generalized slowing in the theta or delta range associated with a significantly diminished α power. Power spectrum analysis is one of the standard methods used for quantification of the EEG. The power spectrum, namely the power spectral density, reflects the ‘frequency content’ of the signal or the distribution of signal power over frequency [68].

For the computation of the auditory evoked responses, the average EEG will be measured time-locked to the sound onset events in the music stimuli, after rejecting any residual noise exceeding 100 μV. P1 (fronto-central positive potential with ~50 ms latency), N1 (fronto-central negative potential with ~100 ms latency), and P2 (fronto-central positive potential with ~200 ms latency) amplitudes and latencies will be measured at the Fz and Cz electrodes [69], and compared pre- and post- intervention.

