To reach the goal of obtaining the above-described neurophysiological outcome measures, we will first pre-process the EEG data as follows. Data will be filtered to remove low frequencies not originating from the brain and to control for interference of the electric current, by means of a generic FIR filter, set up as a bandpass filter, with low cut-off at 0.5 Hz and high cut-off at 45 Hz (because of 50 Hz power line noise). Cerebral signals contaminated by artifacts will be identified and removed. Moreover, independent component analysis (ICA) will be performed. ICA algorithms will be used to detect and isolate artifacts, such as eye blinks, eye saccades, hearth, muscle, line noise, channel noise and others. In this way, the original signal will be decomposed into independent components: we will individuate and discard the components that picked up the artifacts activities and reconstruct a clear signal by using only the remaining components [70]. Further pre-processing steps will include epoch extraction, baseline removal, resampling, re-referencing to low temporal electrodes, and filtering.

To investigate whether slow neural oscillations are reduced and fast neural oscillations are increased post-treatment, the continuous EEG will first be divided into 2-seconds segments, transformed into the frequency domain with fast Fourier transform, inspected for myogenic artifact segments that will be rejected, and then averaged across the segments [71]. Any further exploratory analyses will be specified in the future publication of the findings of this study. Missing data will be treated according to Molenberghs et al. [72].

We will evaluate the music and electrical intervention effects on power spectra of frequency bands measuring EEG at rest and during music listening at T0 (pre-intervention), T1 (post-intervention) and T2 (post-placebo). To this end, we will compare the power spectra between rest and music conditions and across time. The ratio of fast (8–30 Hz, alpha and beta) to slow (2–8 Hz, delta and theta) oscillation amplitude at the midline electrodes (Fz, Cz, Pz, Oz) will be measured [70] and compared pre- and post- intervention using t-tests with cluster-based corrections of the multiple comparison problem. In the case of non-normal distributions, there will be applied mixed-effect ANOVAs or non-parametric equivalents to the parametric tests.

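### The T0 value of the tested primary outcomes is used as a level of time or a pre/post comparator, never as a covariate, which loses precision mainly in between-patient contrasts

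*Protocol article*

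**What the plan says.** The Sample size determination section builds the trial on a repeated-measures ANOVA with condition between subjects "and time (pre-intervention, post-intervention and post-placebo), as within-subject factor". The pre-treatment measurement is therefore one of three repeated levels of the response.

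The Data analysis section applies this approach to the outcomes: repeated-measures ANOVA and post-hoc paired t-tests are "conducted to assess the effects of the treatments over time on N1, P1, and P2 amplitudes and latencies, as well as level of consciousness". The EEG fast/slow ratio is to be "compared pre- and post- intervention using t-tests with cluster-based corrections of the multiple comparison problem".

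Two places name covariates. Under Music stimulation, "drug treatment and doses will be inserted as confounding factors and covariates in the ANOVAs". Under Data analysis, the sequence effect is examined "By including the order of intervention as a covariate". Neither place, nor any other, names the T0 value of the outcome as a covariate.

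The Experimental design and procedures section gives three sequences, each with a different first-period condition: tES+music, sham+noise, and music+sham. All are assessed at T0, T1 and T2.

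**The concern.** When T0 is a level of time, the group-by-time test of the first-period effect is a comparison of change scores. It fixes the slope on T0 at 1, whatever the data show. Adjusting for T0 lets the data estimate that slope, and the residual variance is smaller for every correlation below 1.

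Three features of this trial make the point worth raising. There are only 10 patients per group, and the population mixes VS with MCS and three aetiologies. The central hypothesis is that tES adds to the effect of music, but the combined and music-only conditions are never given to the same patient, so the crossover cannot provide that contrast within patients. And with 10 per group, chance differences at T0 can be large in the one trial that is run.

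**Working it through.** **Inputs.** From the protocol: N = 30 in three groups of 10, f = 0.30, 80% power, test level 0.05. Assumed, because the protocol does not state it: the correlation rho between repeated measurements, taken as equal for all pairs of visits (compound symmetry), with unit variance.

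**Step 1: the plan's own figure.** For the group-by-time interaction with m measurements and k groups, lambda = N·m·f²/(1 − rho), with (k − 1)(m − 1) and (N − k)(m − 1) degrees of freedom.
- m = 2, rho = 0.5: lambda = 30 × 2 × 0.09/0.5 = 10.8, df 2 and 27, power 0.800. This matches the stated 80%.
- m = 3, as the plan describes, rho = 0.5: lambda = 30 × 3 × 0.09/0.5 = 16.2, df 4 and 54, power 0.887. Power of 0.80 with m = 3 would need rho of about 0.38.

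So rho = 0.5 reproduces the sample size only with two measurements. It is a working assumption and not an input of the plan.

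**Step 2: first-period contrast, T0 to T1.** The error variance is 2(1 − rho) for the change score and 1 − rho² with T0 as covariate. The ratio is (1 + rho)/2, which is 0.75 at rho = 0.5. Change-score lambda = 5.4/(1 − rho), df 2 and 27. Adjusted lambda is that value × 2/(1 + rho), df 2 and 26. The last column divides the adjusted lambda by 1.04 to allow for chance imbalance at T0.

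| rho (assumed) | change score | T0 as covariate | same, with allowance |
|---|---|---|---|
| 0.3 | 0.648 | 0.837 | 0.821 |
| 0.5 | 0.800 | 0.903 | 0.891 |
| 0.7 | 0.957 | 0.979 | 0.975 |
| 0.8 | 0.995 | 0.998 | 0.997 |

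The gain is 17 to 19 points at rho 0.3, 9 to 10 at 0.5, about 2 at 0.7 and under 1 at 0.8. A simulation of 5,000 trials at rho 0.5 gave 0.81 and 0.90.

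**Step 3: full crossover model.** Take T1 and T2 with condition and period, the three sequences with 10 patients each, and no carryover. Per patient, the covariance of the two changes from T0 is (1 − rho)[[2, 1], [1, 2]]. With T0 as covariate it is (1 − rho)[[1 + rho, rho], [rho, 1 + rho]]. Generalised least squares at rho = 0.5 gives these contrast variances:

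| contrast | change from T0 | T0 as covariate | reduction |
|---|---|---|---|
| tES+music vs placebo | 0.0462 | 0.0450 | 2.5% |
| music vs placebo | 0.1154 | 0.1050 | 9% |
| tES+music vs music | 0.1385 | 0.1200 | 13% |

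The first contrast gains little because the two mirrored sequences supply it within patients, where T0 cancels. The last gains most because it is made between patients.

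**Step 4: chance imbalance.** The standard error of a T0 difference between two groups of 10 is √(2/10) = 0.45 SD. Given an observed T0 difference, the change score carries (1 − rho) times it into the estimate. At rho 0.5, a one-standard-error imbalance shifts the estimate by 0.5 × 0.45 = 0.22 SD, in favour of the group that started lower.

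**The case against.** Repeated-measures ANOVA on group and time is a recognised, valid analysis, and detailed covariate lists are often left to an analysis plan. The first part stands: nothing here is false or invalid. The second carries less weight, because the article does fix where T0 enters the model and does name covariates.

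A reader might infer that the plan gives up 9 to 10 points of power on its own inputs. The documents do not support that. They state no correlation, rho = 0.5 gives 80% only with two measurements instead of three, and the figure belongs to the first-period contrast (or, similarly, to an effect sustained equally at T1 and T2). The plan does not name the first-period contrast as primary. For the crossover contrast of tES+music with placebo, the gain is close to nil.

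If T0 is a very strong predictor, the change score is already nearly efficient and the gain shrinks, as the rows for rho 0.7 and 0.8 show.

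A reader might also infer that the planned analysis is biased. Under randomisation the change-score comparison is unbiased over allocations; chance T0 imbalance costs precision.

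Finally, the calculation does not cover every primary outcome. GOS-E, DRS and LCF are listed as primary but have no named test, and categorical outcomes go to non-parametric tests.

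**Conclusion.** The point holds as a matter of efficiency for CRS-R, the evoked responses and the EEG fast/slow ratio. Adjusting for T0 is at worst neutral, apart from one error degree of freedom. The benefit is substantial for the first-period comparison if rho is about 0.5 or lower, small at 0.7 and negligible at 0.8. In the full crossover model it is modest for contrasts involving music alone and very small for tES+music versus placebo. It also protects against chance baseline imbalance in groups of 10.

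These sizes rest on compound symmetry, on assumed values of rho, on f = 0.30 for the power figures, and on no carryover for the crossover variances. The pre/post t-tests on the EEG ratio have a further weakness that the figures do not measure: as worded, they do not state a comparison between conditions.

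**What to change.** In Data analysis, for each of these outcomes, fit a linear mixed model to the T1 and T2 values with condition received, period, and the patient's T0 value of the same outcome as covariate. The first-period comparison at T1 then becomes an ANCOVA on T0. Replace the pre/post t-tests on the EEG fast/slow ratio with the same baseline-adjusted contrast between conditions. State the assumed T0-to-post correlation alongside the sample size.

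The cost is a change of wording and one error degree of freedom. T0 is already measured, so no extra visits, data or patients are needed, and the plan already admits covariates into its ANOVAs.

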We also acknowledge some limitations that should be considered for the interpretation of the results. First, since our experimental paradigm provides for tailored salient emotional stimuli (namely preferred music), individual differences on music reward sensitivity might influence the elicited responses. Indeed, prior evidence suggested that individual music reward sensitivity affects both physiological (skin conductance) and neural (mainly dopaminergic mesolimbic reward system) responses (see [78, 79]). A second potential limitation is related to the possible overestimation of the treatment effect size, due to the lack of studies performing this multimodal intervention on DOC patients. Accordingly, in the event of preliminary analyses revealing an effect size significantly lower than predicted, we will consider an extension of the population size. Lastly, given the nature of our target population and intervention, which involves specialised healthcare professionals and specifical equipment, we are unable to blind participants and assessors. All in all, this protocol has a high clinical applicability, it is easy to offer, and it is very motivating for the patients and the caregivers. We, therefore, believe that our findings may help to open new paths in the development of new specific DOC rehabilitation approaches.

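### The article states blinding in two opposite ways, and its reason for not blinding does not reach the cleaning of stored EEG files; this leaves an avoidable risk of bias of unknown size, chiefly in the fast/slow ratio

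*Protocol article*

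**What the plan says.** **Outcomes.** The Data analysis section lists as primary measures "i) power spectra of frequency band extracted from the EEG recordings; (ii) auditory evoked responses, extracted from the EEG recordings", besides the CRS-R. The Discussion counts EEG among the objective measures and presents these as a strength of the trial.

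**Cleaning.** The same section says that "ICA algorithms will be used to detect and isolate artifacts" and then, with the study team as subject, "we will individuate and discard the components that picked up the artifacts activities and reconstruct a clear signal". For the spectra, the 2-second segments are "inspected for myogenic artifact segments that will be rejected, and then averaged across the segments". For the evoked responses, averaging takes place "after rejecting any residual noise exceeding" 100 μV.

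**Blinding.** Experimental design and procedures states that the patients and the examiner are masked in full. The limitations paragraph of the Discussion states "we are unable to blind participants and assessors", and attributes this to the target population and to an intervention "which involves specialised healthcare professionals and specifical equipment".

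**File handling.** Ethical considerations says that outcome data are anonymised once acquired. It does not mention masking of sequence or visit.

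**The concern.** The fast/slow ratio compares 8–30 Hz with 2–8 Hz amplitude before and after intervention. Muscle activity can overlap the 8–30 Hz numerator, so the choice of components and segments to discard can move the ratio without any change in brain activity. If the person choosing knows whether a file is pre- or post-treatment, or which sequence the patient is in, stricter or more lenient cleaning could track the visit. A measure put forward as objective would then depend in part on the observer.

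The article's two statements on blinding do not let a reader tell whether anyone who handles outcomes is masked. The more pessimistic one rests on a reason that does not apply to work done offline on recorded files. The protection that is most easily available for these outcomes is therefore not claimed, although nothing in the stated reason prevents it.

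**Working it through.** The point rests on no figure in the plan, so there is nothing to reproduce. The check compares the statements and then gives an illustration of scale.

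**1. Do the blinding statements agree?** No. One masks patients and examiner; the other says neither participants nor assessors can be masked. If examiner and assessor are the same role, the statements contradict each other. If they are different roles, the article does not say so. Neither statement names the people who process EEG.

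**2. Does the stated obstacle reach EEG cleaning?** The obstacle is the patient population and the staff and equipment needed to deliver the intervention. Component and segment selection is applied to recorded data and needs neither the patient nor the stimulator.

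**3. Does cleaning involve judgement?**

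| Step | Rule stated | Feeds |
|---|---|---|
| ICA component removal | Algorithms isolate; the team picks what to discard; no criterion | Spectra and evoked responses |
| Muscle segment rejection | Segments inspected; no threshold | Spectra |
| Residual noise rejection | Fixed 100 μV limit | Evoked responses |

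The spectral outcome passes through two steps without a stated criterion. The evoked responses pass through one such step and one fixed rule.

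**4. Does anonymisation close the gap?** Only partly. A file without a name can still carry its visit or group, and the article does not say whether it does.

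**5. Scale, under assumed figures.** Let *b* be a systematic shift in SD units caused by cleaning, with no true effect. The rejection rate of a two-sided 0.05 test follows from the noncentral *t* distribution. For two groups of *n*, the noncentrality is *b*√(*n*/2) with 2*n* − 2 df. For a paired test it is *b*√*n* with *n* − 1 df, where *b* is in units of the SD of the paired difference. The plan gives 10 per group and 30 in total. At *b* = 0.3:

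- two groups of 10: 0.3 × √5 = 0.67, 18 df, 9.7%
- paired, *n* = 10: 0.3 × √10 = 0.95, 9 df, 13.6%
- paired, *n* = 30: 0.3 × √30 = 1.64, 29 df, 35.5%

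| Assumed shift *b* (SD) | Two groups of 10 | Paired, n = 10 | Paired, n = 30 |
|---|---|---|---|
| 0 | 5.0% | 5.0% | 5.0% |
| 0.1 | 5.5% | 5.9% | 8.3% |
| 0.2 | 7.1% | 8.8% | 18.5% |
| 0.3 | 9.7% | 13.6% | 35.5% |
| 0.5 | 18.5% | 29.3% | 75.4% |

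These are single tests without correction for multiplicity. The table shows what a given shift would do, not that a shift of any of these sizes will occur.

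**The case against.** The strongest reply is that much of this is read from silence. The text never says that cleaning is manual or visual, and it names algorithms. Assessors in the Discussion may mean the bedside raters. Nothing says that the EEG analysts know the visit or group, and an article may leave the coding of EEG files to a fuller document. All of that stands, so missing detail on masking is not by itself the point. What remains is that the article does take a position on blinding, takes it in two incompatible ways, and defends one of them with a reason that does not cover offline processing of primary outcomes.

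A reader might go further and infer three things that the document does not support:

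- *That the EEG is cleaned by hand by unmasked staff, so the outcomes are biased.* The wording suggests judgement, but the analysts' knowledge of visit or sequence is not stated. Only a risk follows.
- *That the bias favours the hypothesis and affects both EEG outcomes alike.* The Introduction, the Discussion and one part of Data analysis expect slow power to fall, whereas another part of Data analysis expects it to rise, so the favoured direction is not settled. The evoked responses have a fixed amplitude limit, and the muscle mechanism concerns the ratio.
- *That the inflation of the ratio can be put in per cent.* The document gives no muscle share. If one assumes a share of 10–20% of fast amplitude, keeping rather than removing it raises the ratio by 11–25% when amplitudes add linearly, 1/(1 − m), but by only 0.5–2% when independent sources add in power, 1/√(1 − m²). Both contrast keeping all muscle activity with removing all of it, and bias would also need that contrast to differ systematically between visits or groups. No such figure should be quoted.

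**Conclusion.** The concern holds in a limited form. The two blinding statements conflict and must be reconciled. The reason for giving up blinding does not extend to stored EEG files, and cleaning that appears to rest on judgement precedes the primary spectral outcome and, through ICA, the evoked responses. This is an avoidable risk of bias of unknown size and unsettled direction, greatest for the fast/slow ratio. It is not a demonstrated bias.

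The conclusion assumes that discarding components and inspecting segments leaves some human choice, and that the anonymisation described covers identity only. If rejection follows fixed automatic criteria, or if files are already coded for visit and sequence, the risk largely disappears and only the contradiction is left. The point is worth settling before cleaning begins, since masking introduced afterwards would mean cleaning every file again.

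**What to change.** 1. Reconcile Experimental design and procedures with the Discussion: say role by role who is masked, and confine the statement that blinding is impossible to the bedside roles that it really concerns.
2. In Data analysis, state that each EEG file receives a random code hiding patient, sequence and visit before ICA and segment rejection. Recording dates in the file would have to be hidden too, as they reveal the visit.
3. Let the independent researcher who already runs the randomisation hold the key, and open it only after the cleaned data set is locked.
4. If component or segment rejection is in fact done by a fixed criterion, say so and give the criterion, as is already done for the 100 μV limit.

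The cost is a few hours of file handling by a role that already exists, with no new visits or staff and no change to the intervention. Rest and music recordings will remain distinguishable by type. That does not reveal sequence or visit, since both are recorded at T0, T1 and T2.

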**Methods:**

This is a randomised cross-over trial in which a total of 30 participants will be randomly allocated to one of three different combinations of conditions: (i) Music only, (ii) tES only (control condition), (iii) Music + tES. The music intervention will consist of listening to an individually tailored playlist including familiar and self-relevant music together with fixed songs; concerning NIBS, tES will be applied for 20 minutes every day, 5 times a week, for two weeks. After these stimulations two weeks of placebo treatments will follow, with sham stimulation combined with noise for other two weeks. The primary outcomes will be clinical, i.e., based on the differences in the scores obtained on the neuropsychological tests, such as Coma Recovery Scale-Revised, and neurophysiological measures as EEG, collected pre-intervention, post-intervention and post-placebo.

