### Experimental design and procedures

The experimental paradigm is one of the main strengths of the study, as a randomized cross-over design will be used in this trial, including a treatment condition with electric brain stimulation combined with music listening and a placebo condition with sham brain stimulation combined with noise listening. The randomization of the participants to be included in each group will be done using the software “Research Randomizer” (www.randomizer.org). The randomization procedure will be performed by an independent researcher unrelated to the study. The randomization file will be saved in a password-protected online database. This independent researcher will enrol participants and will assign the patients to intervention groups. Both patients and examiner will be fully blinded.

Assessment times of outcome measures will be conducted at admission (T_0_), after the first weeks of post-intervention or post-placebo (T_1_), and after the second two weeks of post-intervention or post-placebo (T_2_) (Fig 1). Patients will be randomized into three groups depending on the order of the stimulation or placebo conditions:

Stimulation-Placebo: Patients receiving tES combined with music stimulation for 2 weeks, 1 week of wash out, then sham stimulation combined with noise (placebo) for other 2 weeks.Placebo-stimulation (combined tES and music): Patients receiving sham stimulation and noise (placebo) for the first 2 weeks, then 1 week wash out, and finally tES and music stimulation for other 2 weeks.Music-placebo: Patients receiving music stimulation and sham stimulation for 2 weeks, 1 week of wash out, then sham stimulation and noise (placebo) for another 2 weeks.

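### T1 and T2 carry fixed treatment labels in the EEG analysis that are reversed for the placebo-first third of patients

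*Protocol article*

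**What the plan says.** The protocol article describes the assessment times in two ways.

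- **Fixed labels.** Under Data analysis, the EEG power spectra, a primary outcome, are to be studied by "measuring EEG at rest and during music listening at T0 (pre-intervention), T1 (post-intervention) and T2 (post-placebo"). The spectra are then compared over time, and the fast-to-slow ratio is compared before and after intervention by t-tests. The Methods paragraph of the abstract gives the same order in prose: "After these stimulations two weeks of placebo treatments will follow, with sham stimulation combined with noise for other two weeks".
- **Labels that depend on sequence.** Under Experimental design and procedures, the assessments fall "after the first weeks of post-intervention or post-placebo (T_1_), and after the second two weeks of post-intervention or post-placebo (T_2"). Three sequences follow. The first is "Patients receiving tES combined with music stimulation for 2 weeks, 1 week of wash out, then sham stimulation combined with noise (placebo"). The second is "Patients receiving sham stimulation and noise (placebo) for the first 2 weeks, then 1 week wash out, and finally tES and music stimulation". The third is "Patients receiving music stimulation and sham stimulation for 2 weeks, 1 week of wash out, then sham stimulation and noise (placebo").

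The Sample size determination section makes condition a between-subject factor and adds "time (pre-intervention, post-intervention and post-placebo), as within-subject factor". It plans 10 patients per group, 30 in all. The Data analysis section also enters the order of intervention as a covariate, in order to see whether sequence affects the outcomes.

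**The concern.** In the second sequence T1 follows placebo and T2 follows tES plus music. The labels in the EEG analysis therefore file those patients' placebo data as active and their active data as placebo. The two combination sequences then pull in opposite directions in any T1-versus-T2 comparison that ignores sequence, and the T0-to-T1 change mixes treated and placebo patients. The combination is the treatment the trial was set up to study, and EEG power is one of its primary outcomes. This is not a detail left to a fuller document: one section states a rule that another section contradicts.

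**Working it through.** **Inputs from the article:** 10 patients per sequence, N = 30, f = 0.30, d = 0.68, power 80%, two-sided alpha 0.05.

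**Assumed, because the article does not state them:** correlation rho between repeated measures 0.5 (range 0 to 0.7 shown below); music-only effect versus placebo dM from 0 to 0.68 SD; combination effect dC = 0.68 SD; outcome SD 1; no period or carryover effect unless stated.

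**The plan's own figure.** For a group-by-time interaction, lambda = f² × N × m / (1 − rho). With 3 groups, m = 2 measurements and rho = 0.5, lambda = 0.09 × 30 × 2 / 0.5 = 10.8 on 2 and 27 degrees of freedom, and power is 0.800. So N = 30 is reproduced, though with two measurements rather than the three time points named. With three, power at N = 30 is 0.887.

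**Expected T1 minus T2 by sequence**

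| Sequence | T1 follows | T2 follows | E(T1 − T2) |
|---|---|---|---|
| 1 (n = 10) | tES + music | placebo | +dC |
| 2 (n = 10) | placebo | tES + music | −dC |
| 3 (n = 10) | music + sham | placebo | +dM |

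**Analysed as labelled and pooled**

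- Sequences 1 and 2, T1 − T2: (10 × 0.68 − 10 × 0.68) / 20 = 0. At 11:9 it is 2 × 0.68 / 20 = 0.068 SD; at 12:8 it is 4 × 0.68 / 20 = 0.136 SD.
- All 30, T1 − T2: (10 dC − 10 dC + 10 dM) / 30 = dM / 3. This is 0, 0.113 or 0.227 SD for dM = 0, 0.34 or 0.68. The combination effect drops out.
- Sequences 1 and 2, T1 − T0: (10 × 0.68 + 10 × 0) / 20 = 0.34 SD, half of dC.
- All 30, T1 − T0: (0.68 + 0 + dM) / 3 = 0.227 to 0.453 SD.

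**Rejection rates.** The SD of a within-patient difference is √(2(1 − rho)), which is 1 at rho = 0.5. Simulated paired t-tests on T1 − T2 as labelled reject in 1.8% of trials for sequences 1 and 2, and in 2.5%, 5.0% and 13.1% for all 30 at dM = 0, 0.34 and 0.68.

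**Coded by treatment received, sequences 1 and 2.** The mean difference is 0.68 SD and the noncentrality is 0.68 × √20 = 3.04 on 19 degrees of freedom, so power is 82%. The period-adjusted contrast (half the difference between sequences 1 and 2 in T1 − T2) has the same expectation, (0.68 + 0.68) / 2 = 0.68, with standard error ½ × √(1/10 + 1/10) = 0.224. The noncentrality is again 3.04, now on 18 degrees of freedom, and power is again 82%.

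**Sensitivity to rho**

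| rho | SD of difference | Power, coded by treatment (n = 20) | Rejection, as labelled (n = 20) | Rejection, as labelled (n = 30), dM = 0 to 0.68 |
|---|---|---|---|---|
| 0 | 1.41 | 53% | 3% | 4% to 10% |
| 0.3 | 1.18 | 68% | 2% | 3% to 11% |
| 0.5 | 1.00 | 82% | 2% | 2.5% to 13% |
| 0.7 | 0.77 | 96% | 1% | 2% to 16% |

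**Period trend.** Suppose every patient improves by p between T1 and T2, for example through spontaneous recovery. The pooled T1 − T2 in sequences 1 and 2 becomes (dC − dC) / 2 − p = −p. Read by the printed labels, that is placebo outperforming the intervention.

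**The case against.** The strongest reply is that the article never says sequences are pooled. It plans a repeated-measures ANOVA with a between-subject factor, speaks of comparing treatments in view of the crossover, and enters order as a covariate. A sequence-by-time term would keep the effect even with the printed labels: 82% power for sequence 1 against sequence 2, and 73% to 85% across all three sequences for dM = 0 to 0.68. The stated sample size is itself reproduced by an interaction test. This stands, and it makes the cancellation conditional.

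It does not remove the defect. The EEG paragraph's t-tests and its comparison over time name no sequence or group term. A covariate main effect alone would not repair a reversed label. Order is also given another purpose, so a real treatment effect surfacing in a sequence-by-time term could be read as an order effect.

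Two further points stand. The pre/post comparison named for the EEG ratio is diluted, not cancelled. The explicit T1/T2 labels concern EEG power only; CRS-R and evoked responses are not tied to them.

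**Conclusion.** The contradiction is real: the printed labels are wrong for 10 of 30 patients on a primary EEG outcome. Its size depends on how the labels are used. Analysed as labelled and pooled, with equal sequences and no period or carryover effect, the combination effect vanishes from T1 − T2 in the 20 combination patients, against about 82% power at d = 0.68 and rho = 0.5 when coded by treatment received. Over all 30 only a third of the music-only effect remains, and T1 − T0 is halved in the combination sequences. A period trend would make the pooled contrast non-zero and could be mistaken for a treatment effect.

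A reader might infer two stronger conclusions that the article does not support. One is that the planned analysis as a whole cancels the combination effect to zero; that requires ignoring sequence, which the article does not state. The other is that the sample size section also miscodes T1 and T2. It names its levels by treatment without tying them to either visit, and read as treatment received they suit every sequence. Its weakness is narrower: condition is made a between-subject factor although all three sequences receive placebo and the placebo-first patients also receive the combination.

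**What to change.** - Reconcile the abstract's Methods paragraph, the design section and the EEG paragraph of Data analysis by labelling T1 and T2 as end of period 1 and end of period 2 only.
- Give each post-baseline record two variables: treatment received in that period (tES + music, music + sham, or sham + noise) and period (1 or 2).
- Test treatment received with period and randomised sequence in the model and patient as the repeated unit, and state that the EEG comparisons follow this coding.
- In the sample size section, replace between-subject condition with randomised sequence, and make treatment received the within-patient factor. The between-subject term should be replaced rather than deleted, since sequence belongs in a crossover model.

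The cost is protocol wording and data-set coding. No further data, visits or patients are needed.
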